## Substudy 3. Cohort study on obstetric pathology.

### Objective/s

The purpose of this study was to test if pregnant patients with COVID-19 have more obstetrical morbidity than those non-infected.

- Determine the variables that are associated with more maternal and neonatal morbidity.
- Quantify the risk of adverse pregnancy outcomes (e.g., miscarriage, stillbirth, growth restriction) and neonatal outcomes (e.g., NICU, prematurity, death, birth defects).

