## Study population and selection criteria

For the characterization of the clinical course of SARS-CoV-2 infection during pregnancy, the pre-study sample size calculation has not been carried out, as registry-based studies generally tend to be comprehensive without involving hypotheses.

Patients eligible for follow-up of target population will be any pregnant woman who is suspected or needs to be ruled out as having a SARS-CoV-2 infection at any time during pregnancy with positive test results for SARS-CoV-2 by PCR.

Information regarding each pregnant woman's demographic characteristics, comorbidities and current obstetric history was extracted from the medical history and the patient interview; subsequently, age and race were categorized according to the classification used by the Center for Disease Control and Prevention (CDC) (17).

For the selection of the control group to be collected in the same database, patients with a negative COVID-19 delivery diagnosed by PCR screening at delivery, or less than 3 days before, were considered.

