### Patients

Case eligibility criteria included individuals with laboratory confirmation of COVID-19 infection, irrespective of clinical signs and symptoms or the result of another serological test. Positive RNA PCR test from maternal nasopharyngeal swabs.

The selection of the control group will be collected in the same database, considering patients with negative COVID-19 delivery diagnosed by PCR screening at the time of delivery or less than 3 days before.

The delivery or deliveries that were treated in this site and that occurred within the same day, before and after the case (maximum 3 per case), are included in the control group. If the case were the last delivery of the day, the first ones of the following day could be recruited. If the case were the first of that day, the last one of the previous day could be recruited.

The data collected will be entered at the time they join the registry.

Delivery monitoring: the *outcomes* include perinatal and neonatal events, which were collected at the time of delivery and the days immediately afterward. These perinatal events included gestational age, type of delivery, presence of prepartum or premature rupture of membranes before delivery, as well as any medical complications (thromboembolic events, admission to ICU, maternal death) and obstetric complications (hemorrhagic events and hypertensive disorders), while neonatal events included the 5-minute Apgar score, the pH of the umbilical artery and possible complications such as admission to the NICU and neonatal death in the follow-up period or intrauterine foetal death. The definitions of obstetric pathology follow the international criteria of the ACOG and RCOG (18-21).

Follow-up after delivery: Patient follow-up is carried out by the local investigator over the phone and the medical history is consulted from the time the patient is discharged up to 6 weeks later in order to detect late postpartum complications related to COVID 19. In the case of the new-born, the follow-up is 14 days by the investigating neonatology department by telephone and consultation of the patient's medical history to detect symptoms of COVID 19 symptoms. Complications recorded in the mother during this period (mastitis, endometritis, pulmonary embolism) as well as neonatal death or readmission of the new-born due to COVID were considered *outcomes* of interest and analysed together with those described above.

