### Statistics

For the descriptive analysis, categorical variables were expressed as absolute and relative frequencies; whereas quantitative ones were expressed as mean and range (minimum-maximum values). Analysis of the possible association of both the characteristics of the patients and the *outcomes* collected with COVID-19 infection is carried out using the Pearson Chi-square test or Fisher's exact test and the Mann-Whitney U test (after checking the absence of normal data using the Kolmogorov-Smirnov test). See sections of Data Quality Plan and sample size. Statistical significance was established with  $P < 0.05$ . All statistical analyses were carried out with SAS 9.4 software.

For each response variable (*outcome*) a multiple logistic regression model has been carried out, refined with the backward conditional stepwise method.

The response variables are those described in the previous section. The subset of explanatory variables is different for each model and is specified in the text.

It will only be of interest the Odds Ratio (OR), its 95% CI and the significance of the “COVID” factor. The information on the rest of the explanatory variables is irrelevant since they only act as adjustment variables.

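### Substudy 3 samples its controls at delivery, so it cannot compare miscarriage between infected and uninfected women, and two of its follow-up outcomes are worded in terms of COVID-19

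*Protocol*

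**What the plan says.** All references are to the protocol, Substudy 3 unless stated.

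- **Objective/s.** The purpose is to "test if pregnant patients with COVID-19 have more obstetrical morbidity than those non-infected". A bullet beneath it is to "Quantify the risk of adverse pregnancy outcomes (e.g., miscarriage, stillbirth, growth restriction", followed by a list of neonatal outcomes.
- **Patients, cases.** "Case eligibility criteria included individuals with laboratory confirmation of COVID-19 infection, irrespective of clinical signs and symptoms". No gestational age and no delivery is required. The registry's own section on study population and selection criteria takes women infected "at any time during pregnancy with positive test results for SARS-CoV-2 by PCR".
- **Patients, controls.** Controls are "patients with negative COVID-19 delivery diagnosed by PCR screening at the time of delivery or less than 3 days before". They are the deliveries at the same site just before and after the case's delivery, at most three per case.
- **Patients, follow-up after delivery.** The mother is followed for 6 weeks "in order to detect late postpartum complications related to COVID 19". The newborn is followed for 14 days for COVID symptoms. Of the newborn's events, "neonatal death or readmission of the new-born due to COVID were considered" outcomes of interest, to be analysed with the delivery outcomes.
- **Statistics.** Each outcome gets a multiple logistic model, of which only the result for the COVID factor is reported. "The response variables are those described in the previous section".

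**The concern.** A comparison of two groups needs an outcome that could happen, and would be recorded, in both. Miscarriage fails the first condition because women become controls only by reaching delivery. Newborn readmission attributed to COVID partly fails the second: a readmission of the same kind would count after an infected mother if it is put down to COVID, and not count after an uninfected one. Maternal complications can happen in both groups, but a follow-up question framed around COVID invites a more careful search, or readier attribution, in cases.

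All three push in the same direction, towards an apparent harm of infection. An analysis plan written later could not repair them fully, because they concern who is enrolled and what is asked at follow-up.

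**Working it through.** Substudy 3 states no sample size, event rate or effect size, so there is no figure to reproduce. The check is to hold each outcome against the entry rules.

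**Step 1. Can the outcome occur in a control?**

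| Outcome | In cases | In controls |
|---|---|---|
| Miscarriage | Possible: entry is by positive PCR at any time in pregnancy | Impossible: entry requires a delivery |
| Stillbirth, growth restriction, prematurity, NICU admission, neonatal death, birth defects | Possible | Possible |
| Newborn readmission attributed to COVID | Possible | Possible but rarely assigned: the mother is PCR-negative, though the newborn can be infected within 14 days |
| Pulmonary embolism, endometritis, mastitis | Possible | Possible |

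Miscarriage also fails on the matching rule. Controls are found by their position around the case's delivery, and a woman who miscarries has none.

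I read the COVID qualifier in the newborn sentence as applying to readmission only. Neonatal death during follow-up is listed without it in the delivery-monitoring paragraph of the same section.

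**Step 2. What would a comparison of miscarriage give?** The following inputs are assumptions, except the ratio, which is the protocol's maximum: n cases, 3n controls, 0 events in controls by design, r events in cases. The two-sided Fisher p-value is then C(n, r) / C(4n, r), because the only table as extreme is the observed one.

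- n = 100, r = 2: 4,950 / 79,800 = 0.062.
- n = 100, r = 3: 161,700 / 10,586,800 = 0.0153.
- n = 300 or 1,000, r = 3: 0.0155 and 0.0156.

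Three events among cases are therefore enough for P < 0.05. This grants three controls even to a case who miscarries. Removing those nine controls at n = 100 gives 161,700 / C(391, 3) = 161,700 / 9,886,435 = 0.0164, which changes nothing.

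If infection had no effect, the chance of at least three miscarriages among cases is the binomial tail P(X ≥ 3):

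| Assumed risk over all cases | 100 cases | 300 cases | 1,000 cases |
|---|---|---|---|
| 0.5% | 1.4% | 19.1% | 87.6% |
| 1% | 7.9% | 57.8% | 99.7% |
| 2% | 32.3% | 94.0% | about 100% |

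The sample odds ratio is infinite in every such table.

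**Step 3. Newborn readmission.** Suppose all-cause readmission were equal, but 1% of case newborns and no control newborns were coded as COVID readmissions. With 5/500 against 0/1,000, Fisher p = 0.004. This only restates the assumed 1% and 0%. It shows the mechanism, not an expected size.

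**Step 4. Which variables are the responses?** The section just before Statistics is the list of primary variables. It mixes outcomes with age, ethnicity, smoking, COVID-19 symptoms and the COVID-19 diagnosis date. It contains neither miscarriage nor newborn readmission, although the remaining variables are in Appendix 5, a separate file that is not shown. The delivery and follow-up outcomes are described one section further back, under Patients.

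**The case against.** **No visible text plans an odds ratio for miscarriage.** The bullet repeats secondary objective 6 of the registry and speaks of quantifying a risk, not comparing it. Miscarriage is absent from the outcomes under Patients and from the visible variable list. This stands, and it limits the point: the fault is an objective that this control group cannot serve, not a planned invalid model. But the bullet sits under a comparative purpose, and the protocol should say that this item will not be compared.

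**Readmission due to COVID is not impossible in controls.** This stands. A newborn of a PCR-negative mother can be infected within 14 days. The comparison is close to circular, not empty.

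**The maternal complications are ordinary obstetric events.** This also stands. The protocol names pulmonary embolism, endometritis and mastitis, does not restrict follow-up to cases, and keeps controls in the same database. A reader might infer that these events are not sought in controls, or that the comparison is meaningless. The text shows neither. What remains is a risk of unequal ascertainment.

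**The reference to the previous section is loose, not a plan to model everything.** A reader might infer that ethnicity, smoking or the diagnosis date will be regressed on COVID status. The neighbouring sentences distinguish outcomes from patient characteristics and call the other explanatory variables adjustment variables, so that reading is not supported. The reference still points to the wrong list.

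**Conclusion.** The point holds in three parts of unequal weight.

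1. **Miscarriage: certain, and independent of any rate.** Selecting controls on delivery fixes their count at zero. Substudy 3 cannot give an infected-versus-uninfected estimate for an outcome its objective names.
2. **Newborn readmission: a real flaw in definition.** The outcome is linked to the exposure, so an odds ratio for the COVID factor would be biased towards harm. The size cannot be derived from the protocol.
3. **Maternal complications: a caution.** The wording could produce unequal detection or attribution. Whether it would depends on how the follow-up question is put at the sites, which the protocol does not show.

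The other outcomes named in the objective are sound in this respect. The p-values and probabilities above rest on assumed risks and case numbers and on three controls for every case; none is a protocol figure. Appendix 5 could hold a cause-neutral readmission field or a definition of miscarriage. That would lower the cost of the change, but would not remove the conflict between the objective and the control definition.

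**What to change.** - **Miscarriage.** Take it out of the Substudy 3 comparison and describe it among cases only. The denominator should be women infected before the gestational-age limit used to define miscarriage, and the protocol should state that limit. Add miscarriage to the objectives and variables of the substudy that reports it. Substudy 2 is the natural place, but neither its objectives nor its visible variables include it now.
- **Follow-up outcomes.** Define newborn readmission and maternal postpartum complications regardless of cause, and record them identically in cases and controls. Keep attribution to COVID as a descriptive sub-field.
- **Statistics.** Replace the reference to the previous section with the perinatal, maternal and neonatal outcomes set out under Patients, so that symptoms, diagnosis date and baseline characteristics are clearly not responses.

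The cost is small edits to the objectives, the follow-up wording and one sentence of the statistics, plus at most one field for all-cause readmission if it is not already collected. A true comparison of miscarriage would need uninfected women sampled at the same gestational age as the case's infection. That is a different and much larger undertaking, and this point does not require it.

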### Design

Longitudinal cohort case study to quantify the obstetrical and perinatal morbi-mortality throughout all hospitals in Spain with a universal, consecutive PCR based screening program.

Recruitment: 1st March 2020 to 1st March 2021. Spanish sites collected in Appendix 1.

### Patients

Case eligibility criteria included individuals with laboratory confirmation of COVID-19 infection, irrespective of clinical signs and symptoms or the result of another serological test. Positive RNA PCR test from maternal nasopharyngeal swabs.

The selection of the control group will be collected in the same database, considering patients with negative COVID-19 delivery diagnosed by PCR screening at the time of delivery or less than 3 days before.

The delivery or deliveries that were treated in this site and that occurred within the same day, before and after the case (maximum 3 per case), are included in the control group. If the case were the last delivery of the day, the first ones of the following day could be recruited. If the case were the first of that day, the last one of the previous day could be recruited.

The data collected will be entered at the time they join the registry.

Delivery monitoring: the *outcomes* include perinatal and neonatal events, which were collected at the time of delivery and the days immediately afterward. These perinatal events included gestational age, type of delivery, presence of prepartum or premature rupture of membranes before delivery, as well as any medical complications (thromboembolic events, admission to ICU, maternal death) and obstetric complications (hemorrhagic events and hypertensive disorders), while neonatal events included the 5-minute Apgar score, the pH of the umbilical artery and possible complications such as admission to the NICU and neonatal death in the follow-up period or intrauterine foetal death. The definitions of obstetric pathology follow the international criteria of the ACOG and RCOG (18-21).

Follow-up after delivery: Patient follow-up is carried out by the local investigator over the phone and the medical history is consulted from the time the patient is discharged up to 6 weeks later in order to detect late postpartum complications related to COVID 19. In the case of the new-born, the follow-up is 14 days by the investigating neonatology department by telephone and consultation of the patient's medical history to detect symptoms of COVID 19 symptoms. Complications recorded in the mother during this period (mastitis, endometritis, pulmonary embolism) as well as neonatal death or readmission of the new-born due to COVID were considered *outcomes* of interest and analysed together with those described above.

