## Definitions

### Definition of case and healthy patient for the study

The result in the PCR test on a sample of nasopharyngeal and/or oropharyngeal swab was considered synonymous with exposure/non-exposure, defining a case as any pregnant woman with a positive result, regardless of the symptoms. Those cases with clinical presentation of COVID-19 were classified according to the WHO division for adults into: mild symptoms, mild-moderate pneumonia, severe pneumonia and septic shock (16).

The recommended samples for diagnosis are samples from the upper respiratory tract: nasopharyngeal and/or oropharyngeal swab.

A healthy patient is considered to have a negative PCR in the absence of symptoms. Patients with positive IgM or IgG serology cannot be included. The absence of serology does not prevent classifying the patient as healthy if the PCR is negative.

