### Definitions of symptomatic and asymptomatic patient

- Acute symptomatic patient: Positive PCR. Manifests any of the symptoms compatible with COVID-19 at the time of the study or analysis or during admission. These symptoms may vary based on new findings.
- Symptomatic patient: Patients with symptoms before 14 days of delivery, even if they no longer have symptoms at the time of delivery.
- Asymptomatic patient: Positive PCR. No symptoms compatible with COVID-19 were observed at the time of the study or analysis.
- Ex-symptomatic or cured patient: Positive or negative PCR. The patient was symptomatic (PCR+) more than 14 days before delivery and no longer has any of the symptoms compatible with COVID-19 at the time of the study or analysis. Patient can be IgM positive or negative, but shall be IgG+ if serology is available
- Symptomatic patient with sequelae: Positive or negative PCR. The patient was symptomatic (PCR+) and has any of the sequelae recognized after COVID-19 at the time of data analysis. These sequelae may vary based on new findings.

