## Informed consent

In accordance with the criteria of good clinical practice, the subjects will be duly informed of all those details concerning their participation in the study and will freely give their consent in writing or orally, recording this fact in their medical records.

Preferably written or oral consent will be sought for cases and controls chosen at random from among pregnant women who have given birth in each centre and who have COVID-19. The patient may sign the consent electronically (See appendix 7).

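### Substudy 3 sets no time window for cases and defines controls by one negative PCR around delivery, so previously infected women can enter the non-infected group and exposure windows are unequal

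*Protocol*

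**What the plan says.** The stated purpose of Substudy 3 (Protocol, Substudy 3, Objective/s) is to "test if pregnant patients with COVID-19 have more obstetrical morbidity than those non-infected".

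Cases (Substudy 3, Patients): "Case eligibility criteria included individuals with laboratory confirmation of COVID-19 infection, irrespective of clinical signs and symptoms or the result of another serological test". The only other requirement is a positive nasopharyngeal PCR; no time window is given. The registry that supplies these women (Study population and selection criteria) enrols on "a SARS-CoV-2 infection at any time during pregnancy with positive test results for SARS-CoV-2 by PCR".

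Controls (Substudy 3, Patients, with near-identical text in Study population and selection criteria) are chosen "considering patients with negative COVID-19 delivery diagnosed by PCR screening at the time of delivery or less than 3 days before". They deliver at the same site on the same or an adjacent day, at most three per case.

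Two general definitions bear on this:
- The definition of a healthy patient requires a negative PCR without symptoms and adds "Patients with positive IgM or IgG serology cannot be included", but then "The absence of serology does not prevent classifying the patient as healthy if the PCR is negative".
- The symptom categories include a recovered group: "Ex-symptomatic or cured patient: Positive or negative PCR", for women who were PCR positive with symptoms more than 14 days before delivery.

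Substudy 4 (Inclusion criteria) rules out women with a positive laboratory test before delivery. Substudy 3 has no such clause.

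**The concern.** A woman who was PCR positive at 20 weeks and is negative at delivery meets the Substudy 3 wording for a case and also for a control. If she is counted as a control, the comparison is no longer infected against non-infected.

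The windows also differ in length. A case may be identified at any point in pregnancy, so a longer pregnancy gives more time to become one. Delivery before 37 weeks shortens that time and can make infection look protective against preterm birth.

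Finally, where infection is first found at delivery, pre-eclampsia, membrane rupture or foetal death may already have begun, and the section does not order outcome after exposure.

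The Substudy 3 Statistics section reports only the COVID odds ratio, its interval and its significance, so any error in the exposure groups goes straight into the reported results.

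**Working it through.** Substudy 3 gives no sample size, outcome rate or expected odds ratio, so there is no figure to reproduce. Both calculations below are illustrations on assumed inputs.

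**1. Previously infected women among controls**

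Assumptions: baseline risk p0 = 8%; a share q of controls was infected earlier and carries the case risk p1.

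Observed OR = odds(p1) / odds((1 − q)·p0 + q·p1).

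For a true OR of 2.0: odds(p0) = 0.08/0.92 = 0.0870, so odds(p1) = 0.1739 and p1 = 0.1481.

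| q | Control risk | Control odds | Observed OR |
|---|---|---|---|
| 1% | 0.0807 | 0.0878 | 1.98 |
| 5% | 0.0834 | 0.0910 | 1.91 |
| 10% | 0.0868 | 0.0951 | 1.83 |

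For a true OR of 1.5 the same shares give 1.49, 1.46 and 1.43. The baseline risk hardly matters: between 3% and 10%, a true OR of 2.0 with q = 10% gives 1.82 to 1.83. With q = 0 the true OR is recovered.

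**2. Unequal windows and preterm delivery, with no true effect**

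Assumptions: constant infection hazard h per week; mean delivery at 34.5 weeks (preterm) and 39.3 weeks (term). The probability of being a case after w weeks at risk is 1 − exp(−h·w).

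*Whole pregnancy at risk (late deliveries).*
- h = 0.001: probabilities 0.0339 and 0.0385, OR 0.876.
- h = 0.002: probabilities 0.0667 and 0.0756, OR 0.874.
- h = 0.005: OR 0.867.

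So about 0.87.

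*Whole recruitment year.* Recruitment opens on 1 March 2020 (Study design), and controls deliver on or next to the case's day. Assume case capture also starts on 1 March 2020. For a delivery d days later, weeks at risk are the smaller of d/7 and the length of gestation. A preterm and a term woman delivering on the same day then have identical windows until d = 34.5 × 7 = 241.5, about 28 October 2020. That is 241.5/365 = 66% of the year. The full difference applies only from 39.3 × 7 = 275 days, about 1 December 2020.

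Let a and b be the case probabilities of a preterm and a term woman delivering on day d. With deliveries uniform over the year, the Mantel-Haenszel OR stratified by delivery day is Σ a(1 − b) / Σ b(1 − a); the preterm share cancels. It equals 0.942 at h = 0.001 and 0.940 at h = 0.005. With exactly three controls per case and an assumed 8% preterm share it is 0.942 and 0.938. So about 0.94.

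If cases and controls are both classified by PCR in the same window at delivery, the null OR is 1.00.

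**The case against.** The strongest reply is that the general Definitions already settle most of this. They call any pregnant woman with a positive PCR a case, so a recovered woman with a known positive belongs with the cases, and controls sit in the same database. They also bar symptomatic and known seropositive women from being healthy. This stands in part: for known positives the overlap may be small in practice, and what remains is mainly undiagnosed infection, which no exclusion based on test results can find. It does not close the gap. The Substudy 3 Patients section does not refer to those definitions, the healthy-patient rule does not name an earlier positive PCR, and serology is optional. Substudy 4 writes the exclusion out; Substudy 3 does not.

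It may also be said that ordering outcomes after exposure can be left to the analysis plan, and that the diagnosis date is collected. That is fair for the analysis detail, but not for the eligibility wording, which the protocol fixes itself.

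A reader might infer four stronger things that the documents do not support:
- That this is the protocol's only comparison. Substudies 1, 2 and 4 also plan association tests. Substudy 4 adds logistic regression in women without an earlier positive test, classified by PCR around delivery.
- That the preterm OR is biased to 0.87 throughout. That ignores the March 2020 start and the near-same-day controls.
- That the controls are themselves infected, because the Informed consent section speaks of "cases and controls chosen at random from among pregnant women who have given birth in each centre and who have COVID-19". This is loose consent wording, not a selection rule; the two sections that select controls require a negative PCR.
- That the primary contrast should be limited to PCR status at delivery. That would narrow the stated objective and concentrate the outcome-before-infection problem in the main analysis.

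**Conclusion.** The point holds as a gap in the eligibility wording with consequences for the estimates. As written, Substudy 3 lets a previously infected woman be a control and compares an open case window with a single test around delivery.

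The first fault pulls the odds ratios towards 1. It is negligible if 1% of controls are affected (2.0 becomes 1.98) and modest at 10% (1.83). The protocol gives no share, so the real size is unknown.

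The second pulls the preterm OR below its true value. The null value is about 0.94 over the recruitment year and about 0.87 for deliveries from roughly December 2020. This rests on a constant infection hazard, uniform deliveries, case capture from 1 March 2020 and the assumed gestational ages. A hazard that moves with the epidemic would change the figures.

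Matching on site and delivery day reduces the second fault but does not remove it, and it does nothing for the first.

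**What to change.** In Study population and selection criteria and in Substudy 3, Patients:

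1. State the time window in which a positive PCR makes a woman a case.
2. Exclude from controls any woman with an earlier positive PCR or, where done, positive serology in this pregnancy, as Substudy 4 already does for laboratory tests.
3. State that a woman with any positive PCR in this pregnancy is classified as a case, whatever her result at delivery.

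In the Substudy 3 analysis definitions:

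4. For all cases, count only outcomes that start after the COVID-19 diagnosis date, and compare with controls still pregnant at that gestational age.
5. Analyse preterm delivery among cases undelivered and below 37 weeks at diagnosis, against controls still pregnant at the same gestational age. By the rule in item 4, a woman already in preterm labour when first found positive does not count as a later event.
6. Report the contrast limited to PCR status at delivery as a sensitivity analysis, not as the primary.

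The cost is small. The diagnosis date is already collected. A few controls and some outcome events drop out, so intervals widen slightly. Undiagnosed earlier infection remains and should be named as a limitation.

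Separately, as an editorial correction, reword the Informed consent sentence so that it does not describe controls as having COVID-19.

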### Primary objective

Collect and analyse COVID-19 cases in pregnant and postpartum women at associated health centres.

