### Inclusion criteria:

- Single or multiple gestations of 24 weeks or more without a positive laboratory test for COVID-19 prior to delivery.
- Delivery in a public or private maternity hospital in Spain with a diagnostic test for COVID-19 using PCR Kits within 72 hours prior to delivery or 24 hours after delivery.
- The presence of comorbidity is not an exclusion criterion (asthma, diabetes mellitus, hypertension-preeclampsia, endocrine disorder, dermatological pathology or other obstetric or medical-surgical pathologies).
- Acceptance by the pregnant woman to participate in the study by means of informed consent for group study.

The result of the PCR test on a sample of nasopharyngeal and/or oropharyngeal swab was considered synonymous with exposure/non-exposure, defining a case as any pregnant woman with a positive result, regardless of the symptoms. Those cases with clinical presentation of COVID-19 were classified according to the WHO division for adults into: mild symptoms, mild-moderate pneumonia, severe pneumonia and septic shock (16).

The recommended samples for diagnosis are samples from the upper respiratory tract: nasopharyngeal and/or oropharyngeal swab.

A healthy patient is considered to have a negative PCR in the absence of symptoms. Patients with positive IgM or IgG serology cannot be included. The absence of serology does not prevent classifying the patient as healthy if the PCR is negative.

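### Substudy 3 limits when the PCR may be taken for controls but not for cases, and leaves out controls first swabbed shortly after birth; this can bias the COVID odds ratio, in a direction that depends on the outcome

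*Protocol*

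**What the plan says.** **Controls.** The Patients section of Substudy 3 builds the control group by "considering patients with negative COVID-19 delivery diagnosed by PCR screening at the time of delivery or less than 3 days before". The registry-wide section on study population and selection criteria has the same rule: "patients with a negative COVID-19 delivery diagnosed by PCR screening at delivery, or less than 3 days before, were considered". Neither mentions a swab taken after birth.

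**Cases.** The same Patients section of Substudy 3 says: "Case eligibility criteria included individuals with laboratory confirmation of COVID-19 infection, irrespective of clinical signs and symptoms or the result of another serological test". It adds that the PCR must be positive but gives no time relative to delivery. At registry level, women are eligible if infection is suspected or has to be ruled out "at any time during pregnancy with positive test results for SARS-CoV-2 by PCR", and the primary objective also covers women after birth: "Collect and analyse COVID-19 cases in pregnant and postpartum women at associated health centres".

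**Substudy 4.** The inclusion criteria of the prevalence study accept deliveries "with a diagnostic test for COVID-19 using PCR Kits within 72 hours prior to delivery or 24 hours after delivery".

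**Setting and estimand.** The Design section of Substudy 3 places it in hospitals with universal, consecutive PCR screening. Its Statistics section names the odds ratio for the COVID factor, with its 95% CI and significance, as the only result of interest.

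**The concern.** The two arms of the comparison enter under different test-timing rules. A woman who delivers before anyone can swab her, and is swabbed a few hours later, is eligible as a case if the result is positive. If it is negative, the literal wording gives her no route into the control group. A case diagnosed earlier in pregnancy needs no swab around delivery at all, so her delivery stays in the analysis however urgent it was.

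Whether a swab is taken before birth depends partly on how fast and how urgently the delivery went. That is close to several listed outcomes: delivery before 37 weeks, abruption, NICU admission and delivery type. Adjusting for maternal covariates in the logistic models cannot bring back deliveries that were never eligible. Because the COVID odds ratio is the sole quantity of interest in this substudy, a controls-only selection of this kind acts directly on the reported result.

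**Working it through.** The protocol gives no event rate, sample size or odds ratio for Substudy 3, so there is no planned figure to reproduce. The check has two parts.

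**1. Who is eligible, by time of first PCR (literal reading)**

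| First PCR | Positive: Substudy 3 case? | Negative: Substudy 3 control? | Accepted by the Substudy 4 test window? |
|---|---|---|---|
| Earlier in pregnancy only | Yes | No | No |
| Less than 3 days before, or at delivery | Yes | Yes | Yes |
| Up to 24 h after birth | Yes (no limit stated) | Not provided for | Yes |

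The third row is the gap.

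**2. How far the odds ratio could move when the true value is 1**

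All inputs are assumptions:
- p = overall outcome risk in non-infected women
- s = share of them swabbed only after birth
- r = outcome risk in that late-swabbed share

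Cases are unrestricted, so their risk is p. Controls lose the late-swabbed share, so their risk is c = (p − s·r)/(1 − s). The apparent odds ratio is [p/(1 − p)] / [c/(1 − c)].

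Preterm birth, p = 7%, so the odds in cases are 0.07/0.93 = 0.0753:
- s = 2%, r = 20%: c = (0.07 − 0.004)/0.98 = 6.73%, OR = 1.04
- s = 5%, r = 20%: c = (0.07 − 0.010)/0.95 = 6.32%, OR = 1.12
- r = 7% (no difference), any s: c = 7%, OR = 1.00
- s = 2%, r = 3.5%: c = (0.07 − 0.0007)/0.98 = 7.07%, OR = 0.99
- s = 5%, r = 3.5%: c = (0.07 − 0.00175)/0.95 = 7.18%, OR = 0.97

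More extreme inputs give more: s = 10% with r = 20% gives c = 5.56% and OR = 1.28, and r = 30% at s = 10% gives c = 4.44% and OR = 1.62. For abruption with p = 0.5% and r = 2%, the OR is 1.07 at s = 2% and 1.19 at s = 5%.

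The same check can be written with k, the risk in late-swabbed relative to other non-infected women, so that c = p/[(1 − s) + s·k]. For a common outcome such as caesarean, take p = 25% and s = 5%:

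| k | 0.25 | 0.5 | 1 | 2 | 3 |
|---|---|---|---|---|---|
| Apparent OR | 0.95 | 0.97 | 1.00 | 1.07 | 1.13 |

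With s = 1% the range over the same k is 0.99 to 1.03. The sign depends entirely on whether k is above or below 1. The size depends on s and on how far k lies from 1.

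**The case against.** A reader might infer that the COVID odds ratios are inflated. The documents do not support that. Women who deliver before a swab include emergencies, but also rapid, uncomplicated vaginal births. Removing the latter raises the caesarean risk among controls and pushes that odds ratio below 1. The protocol has no data on how many women are swabbed late or how they fare. The larger values, such as 1.62, need both a 10% late-swabbed share and a risk among them of 30% against 4.44% in the rest, nearly seven-fold. Universal screening makes such a share unlikely.

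A reader might also infer that Substudies 3 and 4 contradict each other. They do not. Substudy 4 is a cross-sectional prevalence study with its own criteria, and it gives no reason for its 24-hour allowance. It shows only that a post-delivery window is considered workable in this protocol.

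The wording for controls can also be read generously: a swab taken on the labour ward straight after birth may count as taken at the time of delivery. That is a fair reading, but Substudy 4 spells out its allowance in hours and Substudy 3 does not, so sites could apply the rule differently.

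Finally, widening the control window does not make the main comparison symmetric, because cases diagnosed at any time in pregnancy would still be set against controls defined at delivery. This objection stands, and the fix has to meet it. The asymmetry between case and control rules survives all of these points.

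**Conclusion.** Substudy 3 restricts PCR timing for controls but not for cases and makes no provision for controls first swabbed after birth. The odds ratio can be biased as a result. Upward bias is plausible for preterm birth, abruption and NICU admission; downward bias is possible for caesarean. Under universal screening the effect is probably small: for preterm birth, about 1.04 to 1.12 under a true odds ratio of 1 if 2% to 5% of women are swabbed late and 20% of them deliver preterm, no bias if their risk is ordinary, and slightly below 1 if it is lower. This rests on the literal reading of the control rule and on assumed inputs throughout. It is a cheap improvement to the design, and no claim that the results will be wrong in a known direction is justified.

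**What to change.** - In the registry-wide selection criteria and in the Patients section of Substudy 3, accept as controls women with a negative PCR from 72 hours before to 24 hours after delivery, the window Substudy 4 already uses.
- Use the recorded test date relative to birth in both groups. If only dates and no hours are held, state how the window translates into calendar days.
- Add an analysis restricted to cases first detected in that same window. With one window for both groups, this mechanism drops out and a true odds ratio of 1 is returned as 1.00 for any share and any risk of the late-swabbed.
- Report how many women were not eligible as controls for want of a timely test.

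Cost: a wording change in two sections and one extra analysis. The section on safety measures and confidentiality says that laboratory tests are those each site already performs, so no new procedures are needed. The restricted analysis has fewer cases and is less precise, and a few controls swabbed after birth could have been infected around delivery.
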